### TPT

The 3RH regimen uses the child-friendly formulation of rifampicin (R) 75 mg/isoniazid (H) 50 mg as a FDC [31] for eligible child contacts of < 25 kg. This formulation is procured and provided by the CaP TB project, as the NTP has not yet recommended this regimen, but has approved its use in the context of the study. Prescription is based on the body weight dose range as recommended by WHO [32]. The body weight is measured at the TPT initiation visit and at the TPT outcome visit for both models, and in the facility-based model, it is measured at every follow-up visit. For children of 25 kg or more, the adult RH tablet is be provided. For children receiving an antiretroviral treatment with protease inhibitors (as lopinavir/ritonavir), nevirapine or dolutegravir, 6H is used to avoid the drug-drug interaction between R and these antiretrovirals. Along with the TPT, 10 mg of daily pyridoxine (vitamin B6) is given to each child to prevent peripheral neuropathy.

### Study procedures

#### Symptom screening

Both models use the following symptoms [33] to assess if the contact child has presumptive TB or not:
Persistent non-remittent cough > 2 weeksReported persistent fever > 10 daysReduced playfulness/lethargy/fatigueWheezing > 2 weeksNight sweats > 2 weeksDocumented or reported weight loss, loss of appetite, or no weight gain (failure to thrive) in the last monthMalnourishment using Mid-Upper Arm Circumference below 125 mm in children 6 months–5 years old

The presence of at least one of these symptoms requires TB investigations at the health facility.

For HIV-positive children, symptoms of any duration are suggestive of TB and the child is immediately referred to the clinic. HIV testing is proposed for 5–14-year-old children with unknown status using two rapid tests, as per national HIV testing guidance. In the community model, the first test is done in the household and if positive, the confirmation test is done at the health facility as per national guidance.

In case a child presents a sign that is not yet suggestive of TB due to its duration (ex: cough for less than 2 weeks), the screening is repeated after 2 weeks’ time.

In addition to the screening for TB symptoms, CHWs have been trained to identify critical signs for urgent referral in case the child needs to be seen urgently by a clinician. These signs are recommended by the Integrated Management of Childhood Illness Handbook of the WHO [34] and include lethargy or unconsciousness, chest indrawing, difficulty breathing, sunken eyes, drinking poorly or not drinking, seizures, severe wasting, severe pallor, and edema of both feet.

#### Adherence assessment

The adherence is assessed at each follow-up visit in both models of care using specific questions on how many doses were missed in the last 4 days, by counting the number of doses taken reported by the parent/guardian in a TPT treatment card introduced by the study and by verifying empty drug blister packs. Parent/guardian received treatment adherence counseling at TPT initiation and during follow-up based on treatment adherence.

#### Safety assessment

At each follow-up visit, the children are assessed for TPT tolerability by CHW using a standard check list of signs suggestive of hepatitis, peripheral neuropathy, and rash that are classically associated with HR (nausea, loss of appetite, vomiting, jaundice, dizziness, tingling, or burning sensation in the extremities). In every cluster facility, a clinician was trained to act as a safety monitor and examine children with problems of tolerability identified by the CHW. In case of serious adverse events, the safety monitor immediately notifies the event to the country principal investigator who informs the sponsor and the ethics committee of the respective country. All adverse events and serious adverse events are coded using the Medical Dictionary for Regulatory Activities (MedDRA) dictionary (version 22.1, September 2019). On a 6-month basis, a safety data review is done by the study management team that is then reported to the sponsor and scientific advisory committee.

### Sample size calculation

For the sample size calculation, we used an estimated 60% completion rate among the eligible children in the facility-based arm based on a recent systematic review [35] and a 10% difference in the community-based arm, considered to be the minimal clinically relevant difference. We considered a cluster coefficient variability of 50% based on the variation in the number of bacteriologically confirmed index cases between the 20 clusters in the year prior to the intervention. An intra-cluster correlation of 0.01 was used. With these parameters, we would need to include at least 1500 declared child contacts by the index case who would be eligible to the TPT to have a power of 85%. With a minimum of 1500 enrolled child contacts, we could maintain at least 80% of power to detect a difference of 10% in the primary outcome between the two arms assuming the proportion with the primary outcome in the control arm ranges from 60 to 70% and of the cluster coefficient variability varies from 50 to 70%. The type I error rate *α* is conventionally fixed at 0.05%. Based on national household statistics per country [36–38], we make the hypothesis of one child under 5 years per household. Looking at the index case TB registrations in the year prior to the intervention, we estimate that it would be possible to include 1500 contact children in a 15-month period. Research assistants in each cluster supervised that all bacteriologically confirmed index cases registered in the NTP treatment register were screened for study eligibility to achieve adequate participant enrolment to reach sample size.

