### Statistical analysis

#### Primary analysis

The denominator for the analysis of the primary endpoint is the number of child contacts < 5 years and HIV-infected 5–14 years declared by the index case at the facility during the inclusion visit. Since discrepancies can be expected between what is declared by the index case and what is observed during contact screening, a sensitivity analysis will be performed using as denominator the number of children < 5 years of age and HIV-infected children of 5–14 years of age identified during the screening. An additional sensitivity analysis will be performed including only participants that followed all study procedures (per-protocol approach) among the declared and then enrolled child contacts. Dropping out of the cascade of cares and potentially being lost to follow-up can be the consequence of the models of care under evaluation. Therefore, lost to follow-up will be kept in the primary outcome analysis. They will be removed from the sensitivity per-protocol analysis.

A generalized linear mixed model with a binomial distribution and logit link function will be used to perform individual-level analysis adjusting for clustering. The regression model will include the fixed effect of treatment assignation and country and one random-effect for the cluster. A degree-of-freedom correction will be applied (between-within method) to deal with the type I error inflation due to the small number of clusters. The primary analysis will focus on the difference between the two study arms adjusted for country, and a secondary analysis will add an adjustment for unbalanced factors (urban/rural, district size) identified in the baseline assessment. For the analysis of the secondary outcomes, a similar mixed model will be used with the same random effects and correction method, focusing on each endpoint of the cascade of care for initiation and completion of TPT and each endpoint of the cascade of care for TB detection. The same model will be applied for the sensitivity analyses.

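### The stated 85% power and 80% floor leave out the planned small-sample correction: with 17 degrees of freedom, power at 60% vs 70% is about 79–81% (cluster-size CV 50%) or 75.5–78% (CV 70%)

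*Protocol article*

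**What the plan says.** All planning inputs are in the protocol article under Sample size calculation.

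- Control rate: "we used an estimated 60% completion rate among the eligible children in the facility-based arm".
- Effect: "a 10% difference in the community-based arm, considered to be the minimal clinically relevant difference".
- Cluster-size variation: "We considered a cluster coefficient variability of 50" per cent.
- Clustering: "An intra-cluster correlation of 0.01 was used".
- Result: 1500 children "who would be eligible to the TPT to have a power of 85" per cent.

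A robustness statement follows: with 1500 children, "we could maintain at least 80% of power to detect a difference of 10% in the primary outcome between the two arms", where the control proportion "ranges from 60 to 70% and of the cluster coefficient variability varies from 50 to 70" per cent. That section mentions no t distribution and no small-sample allowance.

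Under Primary analysis, the test is a logit mixed model with arm and country as fixed effects and a random effect for cluster. It continues: "A degree-of-freedom correction will be applied (between-within method) to deal with the type I error inflation due to the small number of clusters".

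**The concern.** The same document gives a power figure and the test that the figure should describe, and the two do not match. A between-within correction with 20 clusters raises the critical value from 1.96 to about 2.11 and brings in the extra uncertainty of a variance estimated from few clusters. If the sample size was worked out without this, the stated power is too high for the test that will be run.

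What is at stake is how a non-significant result is read. A reader who believes the type II error is 15% at the minimal relevant difference will take such a result as stronger evidence than it is. The 80% floor matters because 60% control is the plan's own planning value, so the range in which the floor fails is not remote.

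**Working it through.** **Inputs.** From Sample size calculation: 60% vs 70% (the 10% read as an absolute improvement), 1500 children, ICC ρ = 0.01, CV 0.50 or 0.70. From the abstract: 20 clusters, 1:1. Hence 750 children per arm and mean cluster size m = 75. Alpha is taken as 5% two-sided; the text prints 0.05%, which is read here as a unit slip, and it does not state sidedness. No dropout inflation applies, because losses stay in the primary analysis.

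**Design effect.** The article names no formula, so two common ones are used.

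- Standard unequal-size form: DE = 1 + [(1 + CV²)m − 1]ρ. CV 0.5: 1 + (93.75 − 1)(0.01) = 1.927. CV 0.7: 1 + (111.75 − 1)(0.01) = 2.107.
- Relative-efficiency form: DE = [1 + (m − 1)ρ] / [1 − CV²·L(1 − L)], with L = 0.75/(0.75 + 0.99) = 0.431. CV 0.5: 1.74/0.9387 = 1.854. CV 0.7: 1.74/0.8799 = 1.978.

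**Standard error and standardised effect.** SE = √[DE × (0.6×0.4 + 0.7×0.3)/750] = √(DE × 0.0006), and δ = 0.10/SE. At CV 0.5, SE is 0.0340 or 0.0333 and δ is 2.94 or 3.00. At CV 0.7, SE is 0.0356 or 0.0345 and δ is 2.81 or 2.90.

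**Step 1: reproduce the plan's figures with a normal cut-off.** Power = Φ(δ − 1.96).

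- CV 0.5: 83.7% (standard) or 85.1% (relative efficiency), against the stated 85%.
- CV 0.7: 80.3% or 82.7%, against the stated minimum of 80%. Inverting the standard form (pooled variance) at CV 0.7 and 80% power gives N = 1501, almost exactly the stated 1500.

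**Step 2: apply the planned test.** Arm and country are both cluster-level terms, so the between-within degrees of freedom are 20 − 3 = 17 (intercept, arm, country). The critical value is 2.110. Power comes from the non-central t with the same δ. Each range runs from the standard to the relative-efficiency design effect.

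| Control vs intervention | CV | Normal cut-off | t, 17 df |
|---|---|---|---|
| 60% vs 70% | 50% | 83.7–85.1% | 79.1–80.7% |
| 60% vs 70% | 60% | 82.1–84.0% | 77.5–79.5% |
| 60% vs 70% | 70% | 80.3–82.7% | 75.5–78.1% |
| 65% vs 75% | 60% | 85.1–86.8% | 80.7–82.6% |
| 65% vs 75% | 70% | 83.4–85.6% | 78.8–81.3% |
| 70% vs 80% | 50% | 90.0–91.1% | 86.3–87.6% |
| 70% vs 80% | 70% | 87.3–89.3% | 83.2–85.5% |

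Within a given design effect the correction costs about 4–5 points at 60% vs 70% (83.7 to 79.1, 85.1 to 80.7). Leaving country out of the count (18 df) changes little: 79.4–80.9% at CV 50% and 75.8–78.4% at CV 70%.

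**Step 3: simulation check.** 20,000 beta-binomial data sets per setting were analysed by weighted cluster-level regression on arm and country. At 60% vs 70%, power with a 1.96 cut-off was 85.3% (CV 50%) and 82.9% (CV 70%); with t on 17 df it was 80.9% and 78.1%. This stands in for the logit mixed model and is not that model itself.

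**The case against.** Several points on the other side have force.

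- **The figures are not a miscalculation.** They are right for a large-sample calculation, and planning with a normal approximation is common. No formula is named, so its use is inferred from the reproduction. This stands as a limit on the claim. A t-based calculation that ignores the CV would give 82.5–83.3%, but the text says that the CV was used, and this still falls short of 85%.
- **The base-case shortfall is modest.** Power stays near 80%, and part of the distance from 85% down to 79% is the choice of design effect. This stands.
- **The ICC may be before country adjustment.** The calculation spends a degree of freedom on country but credits no variance reduction. If, as an assumption, country absorbed a quarter of the between-cluster variance (ICC 0.0075), power at 60% vs 70% would be about 84–85% at CV 50% and 81–83% at CV 70%, and both claims would essentially hold. The document neither states nor excludes this, so the conclusion is conditional on it.
- **1500 is a minimum.** With 1700 children, power at CV 50% is 81.6–83.2%. That helps a little but does not restore 85%.

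Two stronger readings are tempting. A reader might infer that the 80% floor fails throughout its range; the table shows that it holds at 70% control. A reader might also infer that real power is far lower, because the Limitations section expects extra heterogeneity from urban and two-facility clusters. With an assumed ICC of 0.02, power at CV 50% would be about 62–66%, but the document gives no ICC other than 0.01, so nothing in it supports that value as the likely one.

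**Conclusion.** The stated power does not describe the stated primary test. At 60% vs 70%, the planned test gives about 79–81% instead of 85% at CV 50%, and about 75.5–78% instead of at least 80% at CV 70%. The floor is met or narrowly missed at 60% control with CV 50%, and fails clearly there once the CV reaches about 60%. It is borderline at 65% control with CV 70% and holds at 70% control.

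This rests on two-sided alpha of 5%, exactly 1500 children, 17 degrees of freedom, and an ICC of 0.01 that already nets out country. It does not mean that the analysis is unsound: the correction is there to protect type I error, and the confidence interval will carry the same degrees of freedom. The point should be fixed, but it is a misstatement of power and no reason to redesign the trial.

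**What to change.** Keep the sample size, endpoint and test. In the sample size text:

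1. Restate base-case power as about 80% (60% vs 70%, 1500 children, ICC 0.01, CV 50%, t-test with 17 degrees of freedom).
2. State that power is about 75–78% at 60% control with CV 70%.
3. Limit the 80% floor to control rates near 70%, or, at 65%, to a CV of up to about 60%. A blanket limit of 65% and above would not be safe, since 65% with CV 70% can fall to 78.8%.
4. Say whether the ICC of 0.01 is before or after country adjustment, and name the design-effect formula.

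Rows for larger ICCs would be useful but are optional. The cost is a few lines of wording and a slightly less favourable stated power; no extra participants are needed.

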**Methods/design:**

This multicenter parallel open-label cluster randomized controlled trial is composed of three phases: I, baseline phase in which retrospective data are collected, quality of data recording in facility registers is checked, and expected acceptability and feasibility of the intervention is assessed; II, intervention phase with enrolment of index cases and contact cases in either facility- or community-based models; and III, explanatory phase including endpoint data analysis, cost-effectiveness analysis, and post-intervention acceptability assessment by healthcare providers and beneficiaries. The study uses both quantitative and qualitative analysis methods. The community-based intervention includes identification and screening of all household contacts, referral of contacts with TB-suggestive symptoms to the facility for investigation, and household initiation of preventive therapy with follow-up of eligible child contacts by community healthcare workers, i.e., all young (< 5 years) child contacts or older (5–14 years) child contacts living with HIV, and with no evidence of TB disease. Twenty clusters representing TB diagnostic and treatment facilities with their catchment areas are randomized in a 1:1 ratio to either the community-based intervention arm or the facility-based standard of care arm in Cameroon and Uganda. Randomization was stratified by country and constrained on the number of index cases per cluster. The primary endpoint is the proportion of eligible child contacts who initiate and complete the preventive therapy. The sample size is of 1500 child contacts to identify a 10% difference between the arms with the assumption that 60% of children will complete the preventive therapy in the standard of care arm.

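### The type I error rate is printed as 0.05%, a level at which 1500 children give about 30% power, not the stated 85%

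*Protocol article*

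**What the plan says.** The section Sample size calculation gives all the ingredients in one paragraph. For the control arm, "we used an estimated 60% completion rate among the eligible children in the facility-based arm". The effect is "a 10% difference in the community-based arm, considered to be the minimal clinically relevant difference". On clustering, "We considered a cluster coefficient variability of 50" percent, and "An intra-cluster correlation of 0.01 was used". The resulting sample size and its power are 1500 children and 85%: the count refers to declared contacts "who would be eligible to the TPT to have a power of 85" percent. The paragraph adds that power stays at or above 80% if the control proportion lies between 60% and 70% and the coefficient of variation between 50% and 70%.

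The error rate follows: it "is conventionally fixed at 0.05", with a percent sign directly after the number. The article gives no other significance level. The section Primary analysis specifies the mixed model and the between-within degrees of freedom, but no threshold, sidedness or confidence level that would override the figure. The abstract gives the layout: twenty clusters "are randomized in a 1:1 ratio to either the community-based intervention arm or the facility-based standard of care arm".

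**The concern.** An alpha of 0.05% is 0.0005, one hundredth of the usual 0.05. A threshold that strict needs a far larger trial, yet the same paragraph reports 85% power from 1500 children. One of the two figures must be wrong.

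Alpha is the threshold that the primary comparison is planned around. Taken literally, a p-value of 0.01 would count as non-significant, and a true 10-point benefit, which the article calls the smallest difference of clinical relevance, would be missed about 70% of the time. The matching confidence interval would be at the 99.95% level, which nobody is likely to intend. The trial is open-label, so the threshold should be beyond dispute before outcome data are examined.

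**Working it through.** **Inputs from the article.** Control 60%; difference 10 points, taken as an increase to 70%; 1500 children, so 750 per arm; 20 clusters, 10 per arm, so m = 1500/20 = 75 per cluster; intra-cluster correlation (ICC) 0.01; coefficient of variation (CV) of cluster size 0.5; stated power 85%.

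**Assumptions.** The article does not give the sidedness or the design-effect formula. Two-sided is assumed first and one-sided tried afterwards. Three design effects (DE) for unequal clusters are used:

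- Standard: 1 + ((1 + CV²)m − 1) × ICC = 1 + (1.25 × 75 − 1) × 0.01 = 1.93.
- The same with CV² multiplied by 9/10 for 10 clusters per arm: 1 + (1.225 × 75 − 1) × 0.01 = 1.91.
- Relative-efficiency form: (1 + (m − 1) × ICC) / (1 − CV² × L(1 − L)), with L = 0.75/(0.75 + 0.99) = 0.431. This gives 1.74/0.9387 = 1.85.

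**Step 1: reproduce the 85%.** With the standard design effect:

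- Variance sum: 0.6 × 0.4 + 0.7 × 0.3 = 0.45.
- SE = √(0.45 × 1.9275/750) = 0.0340.
- Effect/SE = 0.10/0.0340 = 2.94.
- Power at two-sided 5%: Φ(2.94 − 1.96) = Φ(0.98) = 0.837.

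The relative-efficiency form gives effect/SE = 3.00 and power 0.851.

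**Step 2: change only alpha.** The two-sided critical value at 0.0005 is 3.48.

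- Standard design effect: Φ(2.94 − 3.48) = Φ(−0.54) = 0.295.
- Relative-efficiency form: Φ(3.00 − 3.48) = Φ(−0.48) = 0.315.

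All variants, as pooled / unpooled variance under the normal approximation:

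| Design effect | Effective n per arm | Power at 5% two-sided | Power at 0.05% two-sided |
|---|---|---|---|
| 1.93 | 389 | 83.4% / 83.7% | 28.8% / 29.5% |
| 1.91 | 393 | 83.8% / 84.0% | 29.3% / 30.0% |
| 1.85 | 405 | 84.8% / 85.1% | 30.8% / 31.5% |

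**Step 3: check the 80% floor.** The worst corner is control 60% and CV 0.7. At two-sided 5% it gives 80.0% to 82.7%, so the article's second power statement also reproduces at 5%. At two-sided 0.05% the same corner gives 25% to 28%.

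**Step 4: try to rescue 0.05%.**

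- One-sided 0.05% (critical value 3.29): 36% to 39%.
- Two-sided, clustering ignored: 72%.
- Two-sided, t reference with 17 degrees of freedom (20 clusters less intercept, arm and country): 15% to 16%. The same t reference at 5% gives 79% to 81%, so the stated 85% evidently comes from a normal approximation.
- Two-sided, unlimited children in the same 20 clusters, standard design effect: SE tends to √(0.45 × 1.25 × 0.01/10) = 0.0237 and effect/SE to 4.22. Power is then capped at Φ(4.22 − 3.48) = 77%, so no number of children reaches even 80%.

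**The case against.** The strongest reply is that this is a misprint that any reader will see through. The sentence calls the level conventional, the convention is 0.05, and the paragraph's own power figures show that 5% was used. On that view the 30% figure proves the slip but describes nothing about the trial as planned. The sentence also sits in the sample size section rather than the analysis section, so the full protocol or the analysis plan may carry the right value.

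Most of this stands. It is very probably a unit slip, 1500 is adequate for 5% on the article's own inputs, and it is unlikely that anyone would test at 0.0005. Three limits should also be granted. A one-sided 2.5% test has essentially the same power as a two-sided 5% test, so the power figure alone cannot settle sidedness. Not stating sidedness or a confidence level is something an article may leave to the analysis plan. And the t-based 15% to 16% should not be set against the stated 85%, because the t reference does not give 85% at 5% either; the fair pair is 83% to 85% against 29% to 31%, both from the normal approximation.

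What does not stand is the step from obvious to harmless. The objection concerns a gap, whereas this is a wrong number printed for the one quantity that sets the decision threshold, and nothing else in the article corrects it. A prespecified threshold should not have to be inferred by working backwards from the power.

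**Conclusion.** The point holds. The printed alpha of 0.05% and the stated 85% power contradict each other: with the article's inputs, power is 83% to 85% at two-sided 5% and 29% to 31% at two-sided 0.05%. The result rests on an effect of 60% to 70%, equal arms of 750 children, an average of 75 children per cluster and a standard allowance for unequal cluster sizes. The design effect, variance form and sidedness were all varied, and none brings 0.05% near 85%. The likeliest explanation is 0.05 with a percent sign added. The error lies in the stated threshold, not in the sample size, and it has to be corrected because it is the only significance level the article gives.

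**What to change.** In Sample size calculation, replace the printed level with 5% (0.05), two-sided. Use the same level for the primary test in the analysis plan, and report 95% confidence intervals. The sponsor should confirm that two-sided was intended, since the power figure fits a one-sided 2.5% test equally well. The cost is one line of wording. The 1500 children, the 20 clusters, the model and the endpoint stay as they are, and the correction should be on record before the analysis.
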